### Participants

#### Study population and sample size

We will recruit CTTH sufferers who meet the diagnostic criteria in the International Classification of Headache Disorders, 3rd Edition (ICHD-3) formulated by the International Headache Society [1]. According to a previous study [11], the proportion of responders (at least 50% reduction in days with headache) was 46% after acupuncture treatment versus 35% after superficial acupuncture (odds ratio, 1.32). In this study, we expect an odds ratio of 1.35 when acupuncture is compared with superficial acupuncture. Assuming a significance level of 0.05, a study power of 0.8, and a correlation of 0.5 between independent variables (including study groups, assessment intervals, and the number of headache days at baseline), 199 participants are required to reject the hypothesis that acupuncture is equivalent to superficial acupuncture. Taking a 10% attrition bias into consideration, we will recruit 218 participants in total, with 109 in each group.

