#### Secondary outcome

The secondary outcome measurements are (1) number of headache days per 4 weeks, (2) the mean intensity of headache recorded by visual analogue scale score and grade of headache intensity per 4 weeks, (3) the reduction of medication intake per 4 weeks, (4) the 36-item short form health survey (SF-36) [20], (5) Hamilton Depression Scale (HAMD) [21] and Hamilton Anxiety Scale (HAMA) [22] results, (6) number of participants with adverse events (AEs) and serious adverse events (SAEs), (7) expectation values of acupuncture treatment, (8) the intensity of the *deqi* sensation.

All participants will be asked to complete a daily headache dairy and return them to assessors by emails, short messages or telephone calls throughout the whole 36-week observation period. The first three secondary outcomes will be extracted from the headache diaries. And the three outcomes followed will be assessed at each visiting time point. All of the above outcome measurements will be assessed at baseline, and at 4, 8, 12, 16, 20, 24, 28, and 32 weeks after randomization. Moreover, the expectation value of acupuncture treatment will be collected at baseline and week 8 after randomization, and the intensity of the *deqi* sensation will be assessed at 5 minutes after each treatment using the Massachusetts General Hospital Acupuncture Sensation Scale (MASS).

Details of AEs and SAEs will be documented during the 36-week period, such as occurrence time, duration, coping methods, and the correlation with treatment. AEs include bleeding, hematoma, fainting, severe pain, local infection, and so on, while SAEs are defined as life-threatening events, leading to significant or persisted disability, resulting in or prolonging hospitalization.

Researchers responsible for recruiting participants and assessors responsible for collecting data must receive training to ensure all of them have the same standards and understand the purpose, contents, and quality control of the trial. Detailed time points of outcome assessments are provided in Fig. 2.

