### Statistical analysis

Primary analysis will be based on intention-to-treat population, including participants with at least one assessment of the primary outcome and one acupuncture session. Per protocol (PP) analysis will be performed to test the robustness of the primary analysis. PP population will include participants receiving at least 12 sessions of acupuncture and be assessed at week 8 and 16.

The primary outcome will be analyzed with a random intercept logistic regression model, taking treatment allocation as a random factor and taking sex, age, and duration of headache as fixed factors. The secondary outcomes (headache days, headache intensity, SF-36, HAMA, HAMD results) will be analyzed using a generalized least squares regression model, with the same covariates as the primary outcome. For the rest of outcomes, we will make pairwise comparisons using a general linear model adjusted for baseline value, age, sex, and disease course. Missing values of the primary outcome will be imputed by the last-observation-carried-forward method. We will run several sensitivity analysis to ensure the robustness of the imputation: first, lost-to-follow-up participants in the acupuncture group will be recognized as nonresponders, whereas those in the superficial acupuncture group will be recognized as responders; second, lost-to-follow-up participants will be counted as responders in the acupuncture group but nonresponders in the superficial group; Third, all lost-to-follow-up participants will be treated as nonresponders. Missing values in the secondary outcomes will be imputed by using the multiple imputation method (*n* = 5).

All confidence intervals will be two-sided 95% intervals comparing acupuncture to superficial acupuncture and all statistical hypotheses will be two-sided tests. Analyses will be performed using the R and Stata programs.

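### The least-squares models for the continuous secondary outcomes omit each outcome's own baseline, and the primary model omits the baseline headache days named in the sample-size paragraph

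*Protocol article*

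**What the plan says.** All references are to the protocol article.

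- **Primary model (Statistical analysis).** The responder outcome gets a logistic model "taking sex, age, and duration of headache as fixed factors". Baseline headache days are not on the list.
- **Main secondary models (same section).** Headache days, headache intensity, SF-36, HAMA and HAMD are analysed by generalized least squares "with the same covariates as the primary outcome". The list carried over is therefore again sex, age and duration of headache.
- **Remaining outcomes (same section).** These are compared "using a general linear model adjusted for baseline value, age, sex, and disease course". Set against the Secondary outcome list, what remains is medication reduction, adverse events, expectation and deqi intensity.
- **Baseline data (Secondary outcome).** After describing the diary outcomes and those assessed at visits, the text states: "All of the above outcome measurements will be assessed at baseline". The Abstract likewise schedules the first five secondary outcomes at baseline.
- **Planning model (Study population and sample size).** The calculation assumes "a correlation of 0.5 between independent variables (including study groups, assessment intervals, and the number of headache days at baseline").

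**The concern.** The baseline level of a symptom count or scale score is commonly one of the better predictors of its later level. Here it is measured for every outcome in the least-squares group, yet it is not named in any of those models. Baseline adjustment goes instead to a residual group that includes deqi intensity, which is scored 5 minutes after each treatment and so has no pre-treatment value, and adverse events, which the Abstract summarises only at the end of follow-up. The allocation of covariates looks misplaced rather than chosen.

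Two things are at stake. For the continuous secondary outcomes, intervals are wider than the collected data allow. For the primary outcome, the variables named when the sample size was set differ from those in the analysis model, so a reader cannot tell which model the trial was planned around.

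**Working it through.** **1. Which outcomes lose their baseline**

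| Outcome | Baseline measured? | Baseline in the stated model? |
|---|---|---|
| Responder at week 16 | Yes (baseline headache days) | No |
| Headache days, intensity, SF-36, HAMA, HAMD | Yes | No |
| Medication reduction, expectation | Yes | Yes |
| Deqi intensity | No | Yes |
| Adverse events | No usable pre-treatment value | Yes |

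Duration of headache most likely means disease course, the term used in the last model. On no reading is it the number of headache days at baseline.

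**2. Continuous secondary outcomes**

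Adjusting for a baseline with correlation r to follow-up multiplies the variance of the arm difference by 1 − r², and the interval width by √(1 − r²). The equivalent sample size is 218/(1 − r²). The document gives no baseline-to-follow-up correlation, so r is assumed.

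| Assumed r | Variance factor | Interval-width factor | 218 act like about |
|---|---|---|---|
| 0.3 | 1 − 0.09 = 0.91 | 0.95 | 240 |
| 0.5 | 1 − 0.25 = 0.75 | 0.87 | 291 |
| 0.6 | 1 − 0.36 = 0.64 | 0.80 | 341 |

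For headache days, the entry rule of at least 15 days per month restricts the baseline range and tends to lower r. As an illustration, truncate a bivariate normal with r = 0.5 at the baseline mean. The retained baseline variance is 1 − 2/π = 0.363 of the original. The correlation becomes 0.5 × √0.363 / √(0.25 × 0.363 + 0.75) ≈ 0.33, and the variance saving falls from 25% to 0.33² ≈ 11%.

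**3. Primary outcome**

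A responder has at least 50% fewer headache days, so baseline already enters the outcome. Simulation assumptions: 109 per arm; baseline days normal with mean 21 and SD 4, limited to 15–28; follow-up days with SD 7, limited to 0–28; responder rates about 0.32–0.36 v 0.45–0.46; logistic models with arm alone or arm plus baseline days; 1,500 runs.

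| Assumed r | Correlation of baseline with response | Power without baseline | Power with baseline |
|---|---|---|---|
| 0 | 0.20 | 0.32 | 0.34 |
| 0.3 | −0.01 | 0.40 | 0.40 |
| 0.5 | −0.17 | 0.46 | 0.48 |
| 0.7 | −0.37 | 0.48 | 0.56 |

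The gain is about 0 to 8 points, and it vanishes where the responder definition happens to cancel the baseline association.

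The gain does not come from a narrower interval. In a second simulation (109 per arm, log-odds slopes of 0.3, 0.6 and 1.0 per SD of baseline), the standard error of the arm log odds ratio was 0.279, 0.279 and 0.277 without the covariate and 0.284, 0.292 and 0.307 with it. Power still rose, by roughly 1 to 5 points, because the adjusted odds ratio is less attenuated toward 1.

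**4. Does the planned size depend on baseline adjustment?**

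The plan's 199 could not be reproduced from its stated inputs. An odds ratio of 1.35 from 35%, two-sided 0.05 and power 0.8, gives 1,476. Applying the repeated-measures factor (1 + (m − 1)ρ)/m − ρ² with ρ = 0.5, which includes a baseline term, still gives 451 at m = 9 assessments.

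A value near 199 does appear for 46% v 35% (624 unadjusted): 624 × (4/7 − 0.25) ≈ 201 at m = 7, and 624 × (4.5/8 − 0.25) = 195 at m = 8. That route replaces the stated odds ratio and treats 0.5 as a correlation between repeated measurements, which the text does not say.

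**The case against.** **Baseline may enter as a response.** The outcomes are measured at baseline and at eight later times, and a least-squares model for repeated measures can use baseline as one of the responses. The article names no visit term and may leave that structure to a fuller document. This lowers certainty, but the text gives a covariate list and does not say that baseline is a response.

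**The gains are assumed.** This stands. No r is given, the 1 − r² factor is measured against a single-time comparison without baseline, and the planned models already contain three covariates that may take up a little of the same variation. The range restriction on headache days also stands.

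**Validity is not at stake.** This also stands. Under randomisation the interval without baseline adjustment already allows for chance imbalance. The loss is one of precision.

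**Stronger readings that do not hold.** A reader might infer that the primary interval is wider because baseline is omitted. In a logistic model the omission attenuates the odds ratio and slightly reduces its standard error. A reader might also infer that the sample size was reduced on the strength of baseline adjustment and that this promised precision is now lost. The paragraph names baseline headache days as a predictor and gives a correlation among predictors. It states no baseline-to-outcome correlation and no variance reduction, and the 199 cannot be traced to one.

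**Conclusion.** The point holds for the continuous secondary outcomes. As written, headache days, intensity, SF-36, HAMA and HAMD are analysed without their own collected baselines, at a cost in variance of about 9% to 36% for assumed r of 0.3 to 0.6, and possibly less for headache days. The section is also inconsistent with itself, because it adjusts for baseline in a group of outcomes some of which have none.

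For the primary outcome the omission is mainly a mismatch between the planning and analysis models. The expected gain in power is small, about 0 to 8 points under the simulated conditions, and the simulations did not include sex, age or duration. The analysis is not invalid, but the change is worth making.

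**What to change.** - In the least-squares models, add the baseline value of the same outcome (headache days, intensity, SF-36, HAMA, HAMD) to sex, age and duration of headache. If baseline is meant to be a response instead, say so and specify the group-by-time term from which the arm contrast is read.
- In the primary logistic model, add baseline 4-week headache days, keeping the three existing covariates. State that the odds ratio is then also conditional on baseline headache days; it is already conditional on the other three.
- For the remaining outcomes, limit baseline adjustment to those with a baseline measurement.
- Align the independent variables listed in the sample-size paragraph with the final primary model.

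The data come from the 4-week baseline diary and the baseline assessments already planned, so no new collection is needed. The cost is analysis wording plus the change in what the primary odds ratio is conditioned on. The article reports recruitment as underway, so the change should be recorded before unblinding.

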**Design:**

A two-armed, parallel-design, patient-assessor blind, randomized controlled trial is underway in China. A total of 218 participants with CTTH will be randomly assigned to the treatment group or the control group in a 1:1 ratio. Participants in the treatment group and control group will receive acupuncture or superficial acupuncture treatments in a fixed prescription of acupoints respectively, for a total of 20 sessions over 8 weeks. The posttreatment follow-up period will be 24 weeks. The primary outcome will be the proportion of responders assessed at week 16 after randomization. The secondary outcomes will include the number of headache days, the mean intensity of headache, the reduction of medication intake, results from the 36-item short form health survey, the Hamilton Depression Scale and the Hamilton Anxiety Scale, the number of participants with adverse events, the expectation value of acupuncture treatment, and the intensity of *deqi* sensation. The first five secondary outcomes will be assessed or calculated at baseline, and at 4, 8, 12, 16, 20, 24, 28, and 32 weeks after randomization. Moreover, the expectation value will be collected at baseline and at week 8 after randomization, the intensity of *deqi* sensation will be assessed at 5 minutes after each treatment and adverse events will be summarized at the end of the follow-up period.

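### The baseline-adjusted general linear model given to all remaining outcomes does not fit two of them: deqi has no baseline, and adverse events are yes/no with no meaningful one (minor)

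*Protocol article*

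**What the plan says.** The Secondary outcome section lists eight outcomes. The Statistical analysis section gives several of them a named model: "The secondary outcomes (headache days, headache intensity, SF-36, HAMA, HAMD results) will be analyzed using a generalized least squares regression model". It then covers what is left in one sentence: "For the rest of outcomes, we will make pairwise comparisons using a general linear model adjusted for baseline value, age, sex, and disease course".

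One of the outcomes left is the "number of participants with adverse events (AEs) and serious adverse events (SAEs"), which is one yes/no value per participant. Another is deqi: "the intensity of the *deqi* sensation will be assessed at 5 minutes after each treatment".

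On the timing of AE assessment the article says two things. The abstract states "The first five secondary outcomes will be assessed or calculated at baseline", and AEs are sixth in the list; it adds that "adverse events will be summarized at the end of the follow-up period". The Secondary outcome section, after the three diary outcomes, states "And the three outcomes followed will be assessed at each visiting time point", which takes in SF-36, the Hamilton scales and AEs/SAEs. It continues "All of the above outcome measurements will be assessed at baseline" and at the later visits.

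**The concern.** A model that adjusts for a baseline value needs an outcome measured before treatment, and a Gaussian linear model suits a roughly continuous outcome. Deqi fails the first condition. AEs fail the second and have no meaningful value for the first.

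This is not detail that an article leaves to the analysis plan. The article names a model and its covariates, and the choice does not suit two of the outcomes it covers. The only other binary outcome, response at week 16, is given a logistic model, so the linear model for AEs looks like a side effect of the catch-all wording.

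What is at stake is the safety comparison of deep with superficial needling, above all the interval for rare events such as SAEs, and a clear rule for comparing deqi, which the Discussion says will get special attention. The primary outcome is not affected.

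**Working it through.** The document gives no figure for these analyses, so there is none to reproduce.

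**1. Which outcomes fall under the rule, and do they have a baseline?** Headache days, headache intensity, SF-36 and the Hamilton scales have their own model. That leaves four:

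| Outcome | When measured | Baseline value? |
|---|---|---|
| Medication reduction | Diaries, per 4 weeks, from baseline | Yes |
| Expectation | Baseline and week 8 | Yes |
| Deqi intensity | 5 minutes after each treatment only | No |
| Participants with AEs/SAEs | Abstract: not among the baseline assessments. Secondary outcome section, read literally: baseline included | Contested |

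AEs are documented over 36 weeks, and under Study design the first 4 of these are the pre-treatment baseline period. A record from that period precedes any needling. It is not a meaningful covariate for needling events such as bleeding or hematoma.

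**2. What happens if the baseline term is kept for AEs?** Suppose every participant has a baseline value of zero. The design matrix (intercept, treatment, age, sex, duration, baseline) then has 6 columns but rank 5. The baseline term is not estimable and drops out. The treatment contrast can still be fitted.

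**3. How does the linear model behave on a 0/1 outcome?**

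Inputs: n = 109 per arm (Study population and sample size), two-sided 0.05, and AE risks that are assumed because the document gives none. With x1 and x2 participants with an event and no covariates:

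- d = (x1 − x2)/n
- s² = [x1(1 − x1/n) + x2(1 − x2/n)]/(2n − 2)
- SE = √(2s²/n)
- interval: d ± t(0.975; 216) × SE

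The probabilities of all pairs (x1, x2) from two Binomial(109, p) arms are summed exactly.

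Type I error with equal risk in both arms:

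| Risk | 20% | 10% | 5% | 2% | 1% | 0.5% | 0.2% |
|---|---|---|---|---|---|---|---|
| Type I error | 0.049 | 0.053 | 0.045 | 0.042 | 0.016 | 0.003 | 0.0001 |

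Coverage of the nominal 95% interval for the risk difference:

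| Risks | 20% v 5% | 10% v 2% | 5% v 1% | 2% v 0.2% | 1% v 0.1% |
|---|---|---|---|---|---|
| Coverage | 0.950 | 0.950 | 0.946 | 0.888 | 0.665 |

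**4. Why does coverage fall?** Mostly because of samples with no event in either arm. Then s² = 0, and the interval shrinks to the single point zero.

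- At 1% v 0.1%: 0.99^109 × 0.999^109 = 0.334 × 0.897 = 0.300, out of a total miss rate of 1 − 0.665 = 0.335.
- At 2% v 0.2%: 0.98^109 × 0.998^109 = 0.111 × 0.804 = 0.089, out of 1 − 0.888 = 0.112.

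An interval built from Wilson score limits does not collapse. With 0 of 109 in each arm, the upper Wilson limit is 1.96²/(109 + 1.96²) = 3.84/112.84 = 0.034, so the difference is reported as 0 ± 3.4 percentage points. Its coverage in both rare-event settings is at least 0.99, which is conservative.

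**5. Does covariate adjustment change this?** A simulation of 10,000 runs, adjusting for age, sex and duration with assumed covariate distributions, gave type I error of 0.050 at 10%, 0.051 at 5%, 0.041 at 2% and 0.014 at 1%. At least one participant had a negative fitted risk in 39% of runs at 10% and in 71% to 91% of runs at 1% to 5%.

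**The case against.** The best defence is that this is one catch-all sentence in a condensed article. The abstract says only that AEs will be summarized, so the authors may intend plain description. An analyst would notice at once that deqi has no baseline and would drop the term. The worst interval failure, a zero-width interval when no events occur, would also be obvious. All of this limits the consequence, but the sentence still names a model and exempts no outcome.

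Four stronger readings are tempting, and the document does not support them.

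- **The comparison cannot be run.** It can. As step 2 shows, a constant baseline column drops out and the treatment contrast remains.
- **The linear model's p-values are too small for sparse AEs.** Step 3 shows the opposite: the test is about nominal from 2% upwards and conservative below. A reader may point to 4 v 0 participants, where the linear model gives p = 0.044 and Fisher's exact test 0.12. That gap mainly shows Fisher's conservatism: its own type I error is 0.023 at 5% and 0.006 at 2%, and the uncorrected chi-square test agrees with the linear model (0.0435). Neighbouring tables do not change sides: 6 v 0 gives 0.013 v 0.029, and 3 v 0 gives 0.082 v 0.247.
- **AEs certainly have no baseline record.** That is certain only for deqi. For AEs the abstract and the Secondary outcome section conflict.
- **A linear model is unfit for deqi, or misstates its precision.** Deqi is a scale score, and nothing shows that a linear model is unsuitable. The article does not say that the ratings from up to 20 sessions will be treated as independent, and how they are summarized may be left to the analysis plan. The shown defect is the missing baseline.

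**Conclusion.** The concern stands as a minor point. The stated rule is wrong for two of the four outcomes it covers. For deqi the baseline covariate does not exist. For AEs/SAEs any baseline record is contested within the article and would not be a meaningful covariate, and a Gaussian linear model is the wrong type for a 0/1 outcome.

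The numerical harm is confined to the interval for rare events: coverage of 0.888 at 2% v 0.2% and 0.665 at 1% v 0.1%, but about 0.95 at 5% v 1% and above. These figures assume 109 per arm with complete data, no covariates, the classical standard error, and the stated risks, none of which comes from the document. If AEs turn out to be common, the linear model's interval for any AE would be acceptable and the problem would remain for SAEs. The primary analysis and the sample size are untouched.

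**What to change.** Change the wording of the Statistical analysis section, before unblinding:

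- **AEs and SAEs:** drop the baseline term. Report the proportion of participants with any AE and with any SAE by arm. Compare them by an exact or binomial method, with a score-based 95% interval for the risk difference.
- **Deqi:** drop the baseline term. Compare arms on either the per-participant mean over sessions or a mixed model across sessions with a participant random intercept, and state which.
- **Expectation and medication intake:** keep the stated model, since both have baseline values.
- **AE timing:** reconcile the abstract with the Secondary outcome section on whether AEs are assessed at baseline.

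The cost is a few lines of text. Data collection, visits and sample size do not change.

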#### Primary outcome

The primary outcome measurement is the proportion of responders at week 16. A responder is defined as a participant with a decrease of at least 50% less headache days during 4 weeks. A participant with a reduction of less than 50% headache days, including anyone with missing data, is defined as a nonresponder. This outcome measurement will be assessed at week 16 after randomization.

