A recent RCT reported that the acupuncture effect can be maintained for 20 weeks after 20 sessions of treatment over 4 weeks, which could be considered as powerful evidence for the existence of a sustained effect produced by acupuncture [43]. In addition, a systematic review indicated that the placebo effect of acupuncture showed a unique pattern according to time, which increased from baseline to 12 weeks and decreased after 12 weeks [44]. Considering the necessity of a relatively long observation period, we will conduct the trial over a period of 36 weeks and make assessments every 4 weeks, which aims to not only evaluate the long-term effect of acupuncture for CTTH, but also distinguish curative effects from placebo effects of acupuncture. However, the long observation period has its limitations. It may increase the rate of patient dropout and we will not know if the patients receive other treatments in the follow-up period. To minimize the potential bias, we formulate the plan to reduce dropout by establishing good communication relationships with participants and maintaining close contacts via telephone calls, text messages and emails during the follow-up period. Moreover, characteristics of the dropouts will be extracted and analyzed, which can help judge whether the results are affected by the bias.

In conclusion, the results of this trial are expected to not only provide clinical evidence of the effectiveness of acupuncture as a painkiller, but also evaluate the duration and intensity of the acupuncture effect for CTTH.

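### The primary endpoint has two incompatible rules for missing week-16 data (nonresponder by definition, last observation carried forward in the analysis), and the article does not say which is primary

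*Protocol article*

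**What the plan says.** Three statements in the protocol article bear on a missing week-16 response.

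- **Primary outcome section.** The missing-data rule is part of the endpoint: "A participant with a reduction of less than 50% headache days, including anyone with missing data, is defined as a nonresponder". The endpoint has a single time point: "This outcome measurement will be assessed at week 16 after randomization".
- **Statistical analysis section, main method.** "Missing values of the primary outcome will be imputed by the last-observation-carried-forward method".
- **Statistical analysis section, sensitivity analyses.** Two extreme-case analyses give the arms opposite outcomes. In the third, "all lost-to-follow-up participants will be treated as nonresponders".

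The same section limits the primary population to randomized participants "including participants with at least one assessment of the primary outcome and one acupuncture session".

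Missing data are expected. The sample size section allows for 10% attrition on 218 participants, 109 per arm. The dropout criteria remove those who do not reach 12 sessions. The Discussion accepts that long follow-up may raise dropout.

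**The concern.** If the endpoint definition is followed, every participant without week-16 data already has a value, nonresponse, and nothing is left to impute. If the analysis section is followed, those participants take their last earlier status, and the rule that defined the endpoint is only a sensitivity check. Each section is clear alone; together they give two primary analyses.

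At stake is which result counts as the pre-specified one. Two analysts working faithfully from this article could report different primary estimates from the same data. If the results fell on either side of 0.05, the article would give no basis for preferring one.

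Carrying forward also fits this endpoint awkwardly. Treatment ends at week 8 and response is judged at week 16. The values available to carry come from weeks 4, 8 and 12, so some are on-treatment responses standing in for a post-treatment one.

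**Working it through.** **Step 1: the rules side by side.** Take a participant who met the response threshold at weeks 4, 8 and 12 and has no week-16 diary.

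- Primary outcome section: nonresponder.
- Statistical analysis section, main analysis: responder, carried from week 12.
- Statistical analysis section, third sensitivity analysis, if the participant is lost to follow-up: nonresponder.

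The rules agree for everyone only if no week-16 data are missing or every carried-forward value is a nonresponse.

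The population sentence does not settle the matter. If the required assessment is the week-16 one, participants missing it are excluded and neither rule has anyone to act on. If it means any 4-week diary period, the two rules conflict as above.

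**Step 2: inputs for size.** The article gives no figure for the effect of missing data, so there is none to reproduce.

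- From the sample size section: 109 per arm and 10% attrition, so 109 × 0.10 = 10.9, about 11 per arm if loss is equal (an assumption).
- Observed responder rates r: 46% and 35%, the earlier study's result quoted there, used for illustration only.
- Carried-forward response rates c (assumed): equal to the observed rates, or 50% in both arms.
- Unequal loss of 5% v 15% and 15% v 5%: hypothetical, not in the article.

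**Step 3: formula.** With loss fraction f, arm rate = (1 − f) × r + f × c, and c = 0 under the nonresponder rule. The gap between the rules (carried forward minus nonresponder) is therefore f_A × c_A − f_C × c_C, where A is acupuncture and C is control.

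**Step 4: results** (differences in percentage points, acupuncture minus control).

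| Loss, A / C | Nonresponder rule | Carried forward, c = 46 / 35 | Carried forward, c = 50 / 50 | Gap |
|---|---|---|---|---|
| 10% / 10% | 41.4 − 31.5 = 9.9 | 46.0 − 35.0 = 11.0 | 46.4 − 36.5 = 9.9 | 0 to 1.1 |
| 5% / 15% | 43.7 − 29.75 = 13.95 | 11.0 | 46.2 − 37.25 = 8.95 | −3.0 to −5.0 |
| 15% / 5% | 39.1 − 33.25 = 5.85 | 11.0 | 46.6 − 35.75 = 10.85 | +5.0 to +5.2 |

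The gap changes sign with the pattern of loss.

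**Step 5: can it cross 0.05?** Take 11 missing per arm and 45/98 v 34/98 observed responders, with an unadjusted pooled two-proportion z test (not the planned model).

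- Nonresponder rule: 45/109 v 34/109, 10.1 points, p = 0.121.
- Carried forward, 5 v 4 carried responders: 50/109 v 38/109, 11.0 points, p = 0.098.
- Carried forward, 7 v 3: 52/109 v 37/109, 13.8 points, p = 0.039.
- Carried forward, 3 v 7: 48/109 v 41/109, 6.4 points, p = 0.335.

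The 5 v 4 split is close to what the observed rates imply (11 × 0.46 = 5.1; 11 × 0.35 = 3.9). The other two splits are hypothetical; they show that crossing 0.05 is possible, not that it is likely.

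**The case against.** The strongest defence is that the intention can be inferred. Because the all-nonresponder rule appears among the sensitivity analyses, carrying forward was probably meant as primary, perhaps with the nonresponder rule kept for those with nothing to carry. Both results are pre-specified, as are both extreme cases. Statisticians are blinded to allocation and have no access to the data during evaluation. With equal 10% loss and the carried rates in the table, the shift is about 1 point at most.

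Much of this stands. It limits the room for a data-driven choice and makes the expected effect modest. It does not remove the conflict: the endpoint definition covers "including anyone with missing data, is defined as a nonresponder" without exception, and no sentence ranks the two rules.

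A reader might also infer more than the article supports:

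- **That the rule moves a planned 11-point difference by 5 points.** The 46% v 35% is the earlier study's result. The plan is an odds ratio of 1.35. From 35%, the odds are 0.35/0.65 = 0.538; × 1.35 = 0.727; 0.727/1.727 = 42.1%, about 7 points. The 5-point gap needs unequal loss that the article never states.
- **That carrying forward favours acupuncture or the long-term claim.** The Discussion cites a placebo effect "which increased from baseline to 12 weeks and decreased after 12 weeks", but also a trial in which the acupuncture effect lasted 20 weeks after treatment. A fading placebo response carried forward could raise the control arm and narrow the difference. Nonresponse is carried forward too, and a participant who leaves before week 4 has no response to carry.
- **That multiple imputation of headache days as a secondary outcome is a further contradiction.** A continuous secondary outcome may properly use a different method from a binary primary one.

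**Conclusion.** The contradiction is established from the text alone and rests on no numerical assumption: the primary endpoint has two incompatible missing-data rules and no stated order between them. An analysis plan that is not shown could not agree with both.

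Its numerical effect is uncertain. It is about 0 to 1 point with 10% loss equal by arm and carried-forward response at the observed rates or at 50% in both arms, and about 3 to 5 points under the hypothetical 5% v 15% losses. More lopsided carried-forward splits would widen the equal-loss figure (7 v 3 of 109 shifts it by 4/109 = 3.7 points). The direction depends on which arm loses more participants and on what is carried, so it cannot be known in advance. The choice would decide the conclusion only for a borderline result, but the primary result should be unambiguous before any data are unblinded.

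**What to change.** Name one primary rule and state it in the same words in the Primary outcome and Statistical analysis sections. Any single choice removes the contradiction. The smallest coherent change is:

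1. Keep the nonresponder rule as primary, since it is already part of the endpoint.
2. Remove last observation carried forward as the primary method, because it carries week 4 to 12 responses to a post-treatment week-16 endpoint.
3. Replace the third sensitivity analysis, then redundant, with multiple imputation of week-16 headache days, for example within arm from baseline and the earlier 4-week counts. Derive responder status from the imputed days.
4. Keep the two extreme-case analyses.
5. In the same edit, say whether the assessment required for the primary population is the week-16 one or any 4-week diary period.

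If carrying forward is preferred instead, strike the missing-data clause from the endpoint definition and say whether headache days or responder status is carried.

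The cost is a few sentences and one extra imputation analysis; multiple imputation is already planned for secondary outcomes. The downside is that the nonresponder rule is itself sensitive to unequal loss: in the table it moves from 5.85 to 13.95 points while carrying forward stays between 8.95 and 11.0. The retained and replacement sensitivity analyses would show this.
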